## 9.0 STATISTICAL CONSIDERATIONS

### 9.1 General Design Issues

Stage 1 of A5225/HiFLAC is a phase I/II dose escalation study of the safety and tolerability of an inuction-consolidation strategy of high-dose fluconazole alone for the treatment of CM in HIV-infected participants. Dose escalation will occur between fluconazole cohorts but not within them. Escalation and determination of the MTD will be based on the rate of DLT, as defined in the Glossary of Study-Specific Terms. When safety has been evaluated in Stage 1, additional participants will be enrolled in Stage 2 to one or more doses at or below the MTD to provide additional information on safety and to identify the optimum (best safety and efficacy profile) dose of fluconazole. If more than one dose is to be evaluated, participants will be randomized between fluconazole dose levels in Stage 2. Decisions about escalation between fluconazole cohorts in Stage 1 will be made after the last enrollee in a cohort has been observed for at least 14 days or until it has been confirmed whether or not that participant has experienced DLT. The decision about which doses to study in Stage 2 will be made after all participants in cohort(s) with acceptable DLT have been followed for at least 10 weeks. The decision rules for Stage 1 and the definition of the MTD are detailed in sections below.

In parallel with the fluconazole escalation and efficacy portions of the study, participants will be randomized to standard treatment with an ampho B-based regimen. During Stage 1, the randomization will be 3:1 between fluconazole and an ampho B-based regimen, with 24 participants enrolled in each of the fluconazole cohorts tested. An additional participant will be enrolled to replace each participant excluded for: (a) not being infected with HIV-1; (b) not having a CM positive CSF culture at entry; or (c) refusal/withdrawal of consent prior to taking any study medication, if the participant's Stage 1 cohort is still open to enrollment. Thus, assuming all three fluconazole cohorts are tested, 24 participants will be treated with ampho B in Stage 1. In Stage 2, an additional 24 participants will be enrolled in each of the fluconazole candidate doses identified in Stage 1 based on their safety and efficacy profiles. The randomization ratio between fluconazole and ampho B-based regimens in Stage 2 will depend on how many doses will be evaluated, with the aim of achieving a total of 48 participants receiving ampho B between Stages 1 and 2.

Because of the need to pause between doses in Stage 1 and to pause long enough to confirm efficacy prior to initiating Stage 2, it is difficult to estimate the duration of accrual on this study. We anticipate that accrual may be completed approximately 1 year after all eligible sites are able to begin enrolling. However, pauses between doses in Stage 1 must be factored in.

### 9.2 Outcome Measures

9.2.1 Primary Outcomes

9.2.1.1 Discontinuation of **study-provided** fluconazole or ampho B, including precipitating and surrounding adverse events.

9.2.1.2 Qualitative and quantitative CSF culture results at entry, week 2, and when conducted thereafter.

9.2.1.3 Survival.

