# GLOSSARY OF STUDY-SPECIFIC TERMS

##### 5FC 5-fluorocytosine

ampho B amphotericin B deoxycholate (in A5225/HiFLAC, the abbreviated name is being used for convenience and is not intended to represent an official name for the drug)

ampho B-based regimen in this study, a regimen that is either ampho B alone or ampho B in combination with 5-fluorocytosine **or fluconazole, according to local standard of care**

CCTG California Collaborative Treatment Group

CM cryptococcal meningitis

CNS central nervous system

CSF cerebrospinal fluid

DLT dose-limiting toxicity: interruption of an induction dose of study-provided fluconazole (i.e., 1200 mg, 1600 mg, or 2000 mg daily) for at least 3 consecutive days as the result of a fluconazole-related toxicity, where the discontinuation was initiated prior to day 14

ECG electrocardiogram

EFV efavirenz

hERG human ether-a-go-go-related gene

HiFLAC High-Dose Fluconazole for Treatment in AIDS-Associated Cryptococcal Meningitis, acronym for A5225

IRIS immune reconstitution inflammatory syndrome

LFCrAg lateral flow cryptococcal antigen (assay)

LP lumbar puncture

MOPS manual of operations

MTD maximum tolerated dose, defined for A5225/HiFLAC as the highest dose of fluconazole that can be safely used [i.e., a dose that results in a ≤ 25% rate of fluconazole dose-limiting toxicity (DLT)].

PML progressive multifocal leukoencephalitis

SIP site implementation plan

SMC study monitoring committee

SoC standard of care

SoE schedule of events (protocol section 6.1)

TEN toxic epidermal necrolysis

TLT treatment-limiting toxicity: a toxicity that results in discontinuation of ampho B-based treatment prior to day 14 and prior to receipt of a total of 8.4 mg/kg ampho B

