SAMPLE SIZE Up to 192 participants (up to 96 in Stage 1 and up to 96 in Stage 2).

POPULATION HIV-infected males and females ≥16 years of age presenting with their first episode of CM.

REGIMEN

Table 1: Stage 1 Regimens

| Cohort | N | Induction Step (Step1)  Daily Dose | Induction Following Ampho B Intolerance Step  (Step 2) | Consolidation Step (Step 3)  Daily Fluconazole Dose | Maintenance Step (Step 4) Daily  Fluconazole Dose |
| --- | --- | --- | --- | --- | --- |
| 1A1 | 24 | Fluconazole  1200 mg | N/A | 400 mg  Or 600 mg with RIF | 200 mg |
| 1B1 | 8 | Ampho B-based regimen;  0.7-1.0 mg/kg ampho B | Fluconazole  400-800 mg daily | 400 mg  Or 600 mg with RIF | 200 mg |
| 2A | 24 | Fluconazole  1600 mg | N/A | 400 mg  Or 600 mg with RIF | 200 mg |
| 2B | 8 | Ampho B-based regimen;  0.7-1.0 mg/kg ampho B | Fluconazole  800 mg daily or maximum locally approved dose | 400 mg  Or 600 mg with RIF | 200 mg |
| 3A | 24 | Fluconazole  2000 mg | N/A | 400 mg  Or 600 mg with RIF | 200 mg |
| 3B | 8 | Ampho B-based regimen;  0.7-1.0 mg/kg ampho B | Fluconazole  800 mg daily or maximum locally approved dose | 400 mg  Or 600 mg with RIF | 200 mg |

1 Enrollment to **Stage 1 ended on x/x/2013**.

Fluconazole dose adjustments based on weight must be implemented at the first dose; after entry, fluconazole dose adjustments in response to toxicities should be implemented on a case-by-case basis (see section 7.4).

Table 2: Stage 2 Regimens

| Cohort | N | Induction Step (Step1)  Daily Dose | Induction Following Ampho B Intolerance Step (Step 2)  Daily Dose | Consolidation Step (Step 3)  Daily Fluconazole Dose | Maintenance Step (Step 4) Daily  Fluconazole Dose |
| --- | --- | --- | --- | --- | --- |
| 4 | 24 | Ampho B-based regimen;  0.7-1.0 mg/kg ampho B | Fluconazole 800 mg daily or maximum locally approved dose | 400 mg  Or 600 mg with RIF | 200 mg |
| 5 | 24 | Fluconazole **1600 mg** | N/A | 400 mg  Or 600 mg with RIF | 200 mg |
| 6 | 24 | Fluconazole **2000 mg** | N/A | 400 mg  Or 600 mg with RIF | 200 mg |
| 7 | 24 | Fluconazole **2000 mg plus Flucytosine xx mg** | N/A | 400 mg  Or 600 mg with RIF | 200 mg |

Fluconazole dose adjustments based on weight must be implemented at the first dose; after entry, fluconazole dose adjustments in response to toxicities should be implemented on a case-by-case basis (see section 7.4). **Note that these dose adjustments are recommended only for study-provided fluconazole.**

A5225 Stages 1 and 2 Overview

Flow Chart

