The CCTG trial demonstrated improved clinical outcomes with increasing doses of fluconazole [Milefchik, 2008]. The composite 10-week overall response rates (success defined as alive and CSF culture negative) for fluconazole with and without flucytosine are shown in Figure 1. Of note, fluconazole alone for 10 weeks at the highest doses (1600 mg and 2000 mg/day) had clinical success rates over 60%, comparable to the overall success seen when ampho B is used for 2 weeks followed by fluconazole at 400 mg daily. As the CCTG trial was small and principally designed to assess the safety of higher dose fluconazole with and without flucytosine, a larger phase II trial is needed to confirm these findings in multiple settings and to assess the potential of an all oral treatment regimen to supplant the standard ampho B-based regimen.

Higher doses of fluconazole have been safely employed in the treatment of CM [Haubrich 1994], histoplasmosis [McKinsey 1996], candidemia [Rex 2003], and coccidioidomycosis [Galgiani 1993]. When higher dose fluconazole (up to 2000 mg daily) has been used alone, few serious toxic side effects have been observed (granulocytopenia 4%, and increased liver enzyme test 2%; see Table 2-1).

Table 2-1: Summary of Toxicity Events, CCTG Trial

| Toxicity | Fluconazole alone  N (%) | Fluconazole plus Flucytosine  N (%) |
| --- | --- | --- |
| Sweating | 6 (12%) | 6 (15%) |
| Tachycardia | 7 (14%) | 7 (18%) |
| Abdominal pain | 8 (16%) | 5 (12%) |
| Constipation | 8 (16%) | 6 (15%) |
| Diarrhea | 10 (20%) | 7 (18%) |
| Nausea | 29 (59%) | 23 (57%) |
| Vomiting | 27 (55%) | 24 (60%) |
| Weight loss | 9 (18%) | 8 (20%) |
| Anemia | 7 (14%) | 1 (3%) |
| Granulocytopenia (< 500) | 2 (4%) | 7 (18%) |
| Thrombocytopenia (<50K) | 0 | 3 (7%) |
| Hepatic enzyme increase (1.5x) | 1 (2%) | 3 (7%) |
| Alopecia | 6 (12%) | 4 (10%) |
| Dry skin | 9 (18%) | 13 (32%) |
| Increased skin pigmentation | 1 (2%) | 1 (3%) |
| Decreased hearing | 3 (6%) | 5 (12%) |

When higher dose fluconazole has been combined with flucytosine, the expected hematological side effects (granulocytopenia 18% and thrombocytopenia 7%) were easily detected by regular monitoring. In the CCTG trial, doses of fluconazole at 800, 1200, 1600, and 2000 mg with and without flucytosine were evaluated. Four dosing cohorts were employed, with participants randomly allocated between treatment cells. The baseline demographics of that study population are presented in Table 2-2.

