## 5.0 STUDY TREATMENT

### 5.1 Regimens, Administration, and Duration

A5225/HiFLAC study treatment is defined as study-provided oral fluconazole or as an amphotericin B deoxycholate-based regimen that could include 5-fluorocytosine **or fluconazole**, according to local standard of care.

Amphotericin B deoxycholate will be administered intravenously; 5-fluorocytosine, when administered, will be administered orally. Neither amphotericin B deoxycholate nor 5-fluorocytosine **or fluconazole for use with amphotericin B deoxycholate** will be provided by the study.

Stage 1**, which has been completed, was** a dose escalation study of daily fluconazole from 1200 mg up to 2000 mg. Dose escalation may end before the 2000 mg dose if the MTD has been identified. There will be up to 4 dosing steps for each participant. The study will include a cohort in which participants will be treated with an amphotericin B deoxycholate-based induction regimen.

Stage 2 is a dose validation study of fluconazole doses tested in Stage 1. When either the MTD of fluconazole is reached or the week 10 visit for the final participant randomized to the 2000 mg/day cohort is completed, all data on all participants, including week 10 data for the final randomized participant, will be reviewed. Before Stage 2 is opened, the protocol will be amended; the specific dose or doses of fluconazole at or below the MTD that is or are to be tested in Stage 2 will be identified.

In Stage 2, participants will be randomized to receive an induction treatment of either an amphotericin B deoxycholate-based regimen or one of up to three doses of fluconazole.

At entry to Step 1 in Stage 1, participants will be randomized to receive a single oral high-dose induction regimen of fluconazole or an amphotericin B deoxycholate-based induction regimen. At entry to Step 1 in Stage 2, participants will be randomized to receive either one of up to 3 high doses of fluconazole or to receive an amphotericin B deoxycholate-based regimen. The fluconazole doses listed below are for those participants who enter the study weighing ≥ 60kg. Doses for participants weighing < 60 kg at entry must be modified in the induction step only. The modified regimens for these participants are presented in section 7.4.2, under Fluconazole Dose Modifications.

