6.3.7 Study Treatment Modifications

All modifications to ampho B-based regimens or to study-provided fluconazole, including initial doses, participant-initiated and/or protocol-mandated interruptions of 2 or more consecutive days, any modifications, and any permanent discontinuation of treatment will be recorded on the CRFs at each visit and keyed within 48 hours. Participant-initiated and protocol-mandated interruptions include both inadvertent and deliberate interruptions of the ampho B-based regimens or of study-provided fluconazole.

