11.4.2 Reporting Requirements for this Study

The SAE Reporting Category, as defined in Version 2.0 of the DAIDS EAE Manual will be used for this study. The study agent for which expedited reporting is required is study-provided fluconazole.

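### The primary safety outcome and the DLT definition were not extended to flucytosine when Cohort 7 was added, so a flucytosine-only stop is not scored on either

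*Protocol*

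**What the plan says.** The Schema's table of Stage 2 regimens gives Cohort 7 as fluconazole "2000 mg plus Flucytosine xx mg", N = 24. Section 3.0 also describes a cohort on fluconazole plus flucytosine. Four provisions that decide what counts as a treatment-related safety event do not mention this combination:

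- **9.2.1.1 (primary outcome):** discontinuation of study-provided "fluconazole or ampho B, including precipitating and surrounding adverse events".
- **Glossary, DLT:** "interruption of an induction dose of study-provided fluconazole" for at least 3 consecutive days, caused by a fluconazole-related toxicity and begun before day 14. The companion term, TLT, applies to ampho B-based treatment only.
- **5.1:** "study treatment is defined as study-provided oral fluconazole or as an amphotericin B deoxycholate-based regimen". Flucytosine appears there only as a possible part of the ampho B-based regimen.
- **6.3.7:** "All modifications to ampho B-based regimens or to study-provided fluconazole" go on the CRF. Flucytosine is covered when given with ampho B, but not when given with fluconazole.

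Other provisions do reach flucytosine toxicity in Cohort 7:

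- Sections 6.3.9 and 6.3.13 require Stage 2 sites to record Grade 3 or higher toxicities, laboratory toxicities from a lower grade, and toxicities that lead to a change in treatment.
- Section 6.3.5 records the start or stop of antifungals other than ampho B and study-provided fluconazole. It asks for a flucytosine dose only when the drug is given with ampho B.
- Section 9.2.2.5 makes Grade 3 and 4 events and dose modifications secondary outcomes.
- Section 9.5.2 compares Grade 3 and 4 events between doses or drugs with Fisher's exact test.

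**The concern.** The protocol itself links the added harm of this arm to flucytosine. Section 2.1.2 describes its marrow toxicity, and Table 2-1 shows more granulocytopenia and thrombocytopenia with flucytosine than without. Stopping flucytosine while fluconazole continues is one way such an event could be handled, and it is the one that 9.2.1.1 and the DLT definition cannot register. The same toxicity scores if fluconazole also stops and does not score if only flucytosine stops.

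Objective 1.2.2 uses safety and efficacy data from this study to choose a regimen for the next trial. A primary safety count that is incomplete for one arm only makes the comparison with fluconazole alone uneven on that outcome.

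**Working it through.** **1. The plan's own figures.** Section 9.3.2 gives the chance of at least one event at a true rate of 5% as 64% in 20 and 87% in 40 participants. 1 − 0.95^20 = 0.6415 and 1 − 0.95^40 = 0.8715, so both reproduce. The Table 2-1 percentages reproduce from the Table 2-2 denominators: fluconazole alone 9 + 16 + 16 + 8 = 49, with flucytosine 8 + 8 + 16 + 8 = 40. Granulocytopenia is 2/49 = 4.1% against 7/40 = 17.5%. Thrombocytopenia is 0/49 against 3/40 = 7.5% (printed as 7%).

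**2. Expected events in Cohort 7 (n = 24).**

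| Event | Rate | Expected in 24 | P(at least one) |
|---|---|---|---|
| Granulocytopenia | 0.175 | 24 × 0.175 = 4.2 | 1 − 0.825^24 = 0.99 |
| Thrombocytopenia | 0.075 | 24 × 0.075 = 1.8 | 1 − 0.925^24 = 0.85 |

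On fluconazole alone, 24 × 2/49 gives about 1.0 granulocytopenia case. The two rows should not be added, since one participant can have both events.

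**3. Events not scored on 9.2.1.1.** Let s be the share of granulocytopenia cases that lead to stopping flucytosine alone. The documents do not give s; 0.25 to 1 is an assumption. Unscored stops = 24 × 0.175 × s:

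- s = 0.25: 1.05
- s = 0.5: 2.1
- s = 1: 4.2

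**4. Effect on the arm's rate.** Let b be the rate of fluconazole discontinuation, also assumed, and independent of the flucytosine stops. The primary outcome scores b. The any-component rate is 1 − (1 − b)(1 − 0.175s).

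| b (scored) | s = 0.25 | s = 0.5 | s = 1 |
|---|---|---|---|
| 5% | 9.2% | 13.3% | 21.6% |
| 10% | 13.9% | 17.9% | 25.8% |
| 20% | 23.5% | 27.0% | 34.0% |

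For scale only, Section 9.3.1 treats up to 25% DLT as acceptable. That benchmark is for DLT, not for discontinuation of any component.

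**5. What the secondary comparison can show.** Exact Fisher power at one-sided 0.05 for 20% vs 40% with 24 per group is 33%, close to the 34% in Table 9-3. The same method for 4.1% vs 17.5% gives about 25% with 24 vs 24, and about 45% with 48 on fluconazole alone (both stages) vs 24 in Cohort 7. This assumes that the granulocytopenia cases are graded 3 or 4.

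**The case against.** The strongest reply is that the trial as a whole does see these events. ANC and platelets are measured at scheduled visits, the toxicity is recorded, the flucytosine stop goes on the CRF as other antifungal therapy, and Grade 3 and 4 events are compared between arms. All of that stands. A reader might infer that a flucytosine stop for marrow toxicity counts nowhere, or that Cohort 7 is bound to come out falsely as safe as fluconazole alone. The documents support neither. The gap lies in 9.2.1.1 and the DLT count, and objective 1.2.2 does not rest on 9.2.1.1 alone. The secondary comparison does not close the gap, because its power at these rates is low and 9.2.2.5 speaks of either agent without naming a drug.

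A reader might also extend the point to Section 11.4.2: "The study agent for which expedited reporting is required is study-provided fluconazole". That does not belong here. The sentence leaves out ampho B as well, the scope of the reporting category depends on an external manual, and the choice of agent changes no counted outcome.

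The size is uncertain. Table 2-1 counts toxicities and not drug stops, it pools four fluconazole doses, and Cohort 7's flucytosine dose is still a placeholder. In the same table anemia runs the other way (14% alone, 3% with flucytosine). Section 7.1 directs a fluconazole reduction for any Grade 4 toxicity. That would enter the fluconazole modification record, though a reduction is not a discontinuation. These points are why the result is given as a range.

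Counting any component gives a combination arm more ways to score, and following the backbone drug alone is a defensible choice. Reporting both answers this. Finally, the Stage 2 text is visibly unfinished (Table 5-2 still leaves the doses open) and an amendment is foreseen before Stage 2 opens. That makes the correction easy; it does not make it unnecessary.

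**Conclusion.** The point holds as a gap in the primary safety count for one arm. As written, a Cohort 7 participant who stops flucytosine for marrow toxicity and continues fluconazole has neither a primary discontinuation event nor a DLT. On that outcome the arm can look safer than it is. At the Table 2-1 rates about 4.2 granulocytopenia cases are expected in 24 participants, and about 1 to 4 of 24 would go unscored if 25% to 100% of them led to stopping flucytosine alone. That share is an assumption, and the rates come from an earlier trial that pooled several fluconazole doses. The toxicity remains visible in the adverse event data and in a low-powered secondary comparison. A distorted regimen choice is therefore a risk and not an established result.

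**What to change.** - Reword 9.2.1.1 to discontinuation of any component of the assigned induction regimen (fluconazole, flucytosine or ampho B). Report it per component and for any component, so that the fluconazole-only comparison is kept.
- Name flucytosine in Cohort 7 in 6.3.7 and 9.2.2.5, so that its modifications and discontinuation are recorded and analysed like those of the other study drugs.
- Reconcile the definition of study treatment in 5.1 and the DLT definition in the Glossary with the Cohort 7 regimen. This concerns what is counted and recorded; the dose and the clinical rules are for the study team to settle.

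The cost is protocol wording and one added drug on an existing CRF page; start and stop are already captured under 6.3.5. The stated safety of Cohort 7 may look less favourable, and a combination arm has more components that can score, which the per-component report makes visible. The change should be made before Cohort 7 enrols, since flucytosine dose changes that are not collected as they occur may be hard to recover later.

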9.2.2 Secondary Outcomes

9.2.2.1 Results of the neurological examination (at study entry and at weeks 2, 10, 24, at progression of symptoms, and at the time of premature treatment or study discontinuation) and of functional status evaluation (prior to onset of current CM illness, at study entry, at week 10, and at time of premature treatment or study discontinuation).

9.2.2.2 Length of hospitalization and number and nature of hospital readmissions.

9.2.2.3 Recurrence/relapse of CM based on clinical presentation.

9.2.2.4 CNS IRIS.

9.2.2.5 Additional safety parameters including: Grade 3 and 4 adverse events; dose modifications; duration of temporary treatment interruptions; permanent discontinuation of either agent.

9.2.3 Exploratory Outcomes (to be described in separate analysis plans)

9.2.3.1 Pharmacology (see section 10.0).

9.2.3.2. Antifungal drug susceptibility of cryptococcal isolates.

9.2.3.3 Ability of LFCrAg assay to detect cryptococcal antigen in stored urine, serum, plasma, and CSF.

### 9.3 Sample Size and Criteria for Stages 1 and 2

9.3.1 Stage 1

The team feels that standard dose (400 mg/day) fluconazole would have about 5% DLT as defined in this study. To avoid the toxicity and difficulty of administration of ampho B, the team feels that ≤25% DLT would be acceptable. In the international setting and in participants with HIV and AIDS, the team also has concluded that there likely will be up to a 15% very early mortality rate in any cohort due to CM and/or HIV, not to the dose of fluconazole. Including participants who received very little fluconazole in safety evaluations to determine dose escalation could bias the evaluation either to be too high (if early deaths without toxicity are considered to be DLTs) or too low (if early deaths without toxicity are included in the denominator of the DLT rate). Thus, for primary safety evaluations, very early deaths (prior to Day 4) will not be included in the decision rule whether they experienced a DLT prior to early death or not [French, 2002; Okongo, 1998; Hakim, 2000; van der Horst, 1997; Brouwer, 2004; Pappas, 2004; Bicanic, Meintjes, et al, 2008; and Milefchik, 2008]. Should more than 6 very early deaths be seen in a cohort, enrollment to the cohort will by paused while the team evaluates the events carefully in conjunction with the SMC to consider if there should be study modifications. Secondary evaluations prior to escalation will include all subjects in a failure-time analysis of DLT with early deaths censored if DLT did not occur prior to death.

The dose escalation rule to be used in Stage 1 is:

- 0-3 DLTs; escalate to the next higher dose.
- 4-9 DLTs; do not escalate. This is the MTD.
- > 9 DLTs; the prior dose is the MTD.

Should > 9 DLTs be observed before a cohort is fully accrued, accrual to that cohort will be suspended pending review. The derivation of this rule is based on calculations for a wide range of potential evaluable sample sizes, escalation rules, and scenarios about the rates of DLT at the three fluconazole doses. The following table provides the study-wide operating characteristics of this rule for an example of DLT rates across the three doses if there are 20 or 22 subjects evaluable at each dose, where the “average” DLT was calculated as the weighted average of the underlying rates of DLT.

Table 9-1

| True DLT  1200,1600, 2000 | Prob 1200 Is  > MTD | Prob  1200 Is MTD | Prob  1600 Is MTD | Prob 2000 Is MTD | Average  DLT |
| --- | --- | --- | --- | --- | --- |
| N=20/dose |  |  |  |  |  |
| 0.05, 0.10, 0.20 | 0.000 | 0.016 | 0.139 | 0.845 | 0.184 |
| 0.10, 0.20, 0.30 | 0.000 | 0.142 | 0.542 | 0.316 | 0.217 |
| 0.20, 0.30, 0.40 | 0.010 | 0.625 | 0.338 | 0.026 | 0.237 |
| N=22/dose |  |  |  |  |  |
| 0.05, 0.10, 0.20 | 0.000 | 0.022 | 0.184 | 0.794 | 0.178 |
| 0.10, 0.20, 0.30 | 0.000 | 0.189 | 0.588 | 0.223 | 0.203 |
| 0.20, 0.30, 0.40 | 0.020 | 0.710 | 0.260 | 0.010 | 0.224 |

Thus, for example, if 22 participants are evaluable at each dose level and the underlying true DLT rates are 10, 20 and 30% at 1200, 1600, and 2000 mg doses, there is a 19% chance that 1200 mg will be found to be the MTD, a 59% chance that 1600 will be found to be the MTD, and a 22% chance that 2000 will be found to be the MTD in Stage 1. Stage 2 will provide additional information on safety that will refine these findings.

Assuming exclusion of up to 15% very early deaths from a cohort, accrual of 24 participants at each dose level will yield 20-22 evaluable participants at each fluconazole dose level. Application of the same escalation rule above regardless of the sample size within this range provides consistent escalation probabilities and adjustment to the rule to reflect the number of evaluable participants is not necessary. The dose rule also maintains an average DLT below 25% given the scenarios presented in Table 9-1 should a dose level have more (or fewer) evaluable participants than 20-22. Additionally, as noted previously, DLT will also be evaluated with all participants using a censored approach.

To provide additional detail on this component of the study, the following tables show the within-cohort probabilities of escalation, determination that a current dose is the MTD, or that the prior dose is the MTD for N=20 or 22 evaluable participants at a dose and a range of true underlying rates of DLT.

Table 9-2

|  | .05 | .10 | .20 | .30 | .40 | .50 |
| --- | --- | --- | --- | --- | --- | --- |
|  |  |  |  |  |  |  |
| N=20 |  |  |  |  |  |  |
| Prob(Escalate) | .984 | .867 | .411 | .107 | .016 | .001 |
| Prob(this MTD) | .016 | .133 | .579 | .780 | .580 | .250 |
| Prob(prior MTD) | .000 | .000 | .010 | .113 | .404 | .748 |
|  |  |  |  |  |  |  |
| N=22 |  |  |  |  |  |  |
| Prob(Escalate) | .978 | .828 | .332 | .068 | .008 | .000 |
| Prob(this MTD) | .022 | .172 | .662 | .840 | .617 | .261 |
| Prob(prior MTD) | .000 | .000 | .006 | .092 | .376 | .738 |
|  |  |  |  |  |  |  |

Simultaneous randomization to an ampho B-based regimen during Stage 1 will provide approximately 24 concurrently treated participants for preliminary information on underlying safety, mortality, and efficacy with this arm in an international multi-center setting. This will also ensure that participants in the combined ampho B data span the time of accrual to fluconazole, and reduce bias that might occur should all participants receiving ampho B be accrued only during Stage 2 when sites and participants are aware of the general outcome of Stage 1.

The rate and nature of deaths on Stage 1 will be carefully reviewed on an on-going basis. As noted below, should more than 6 very early deaths be seen in a fluconazole cohort, the team will evaluate the events carefully in conjunction with the SMC to consider if there should be study modifications. There is a 6% chance of a review being triggered if the true early mortality rate is 15% as anticipated, a 61% chance of review if the underlying rate is 30%, and a 90% chance of a review being triggered if the underlying rate is 40%.

Stage 1 can provide preliminary guidance on efficacy for the choice of cohorts to move to Stage 2. With 20-22 subjects with evaluable quantitative culture results over time per group, a difference in mean change in Cryptococcus (expressed as log10 CFU/ml CSF/day) of about 80% of the standard deviation of the measure can be detected with 90% power using a relaxed one-sided 0.10 alpha-level test. For example, if EFA (early fungicidal activity defined as the change from day 0 to day 14) is -0.30 with a standard deviation (s.d.) of 0.15 log10 CFU/ml CSF/day, an increase in the clearance to about -0.42 can be detected.

We recognize that the many neurological complications of CM may obscure drug-related ones. We will monitor participants for unusual neurological manifestations of CM that might be attributed to fluconazole. With 20 (22) evaluable participants, there is a 64% (68%) chance of seeing at least one episode of a completely unexpected unacceptable event that has a true underlying rate of occurrence of 5%. Should we see one or more DLTs associated with cardiac toxicity at a dose level, a targeted review will be triggered. This will happen with 88% probability if the underlying rate of cardiac toxicity is 10%. Should we see 2 or 3 DLTs in 20-22 participants at a dose level, and 2 of 2 or 2-3 of 3 are associated with hepatic toxicity, a targeted review will be performed before the dose can be escalated to the next level. As noted in 9.3.2, the nature and rates of all events will be evaluated prior to accepting any dose for further testing in Stage 2.

9.3.2 Stage 2

The decision about which doses will be chosen for testing in Stage 2 will be based on: Stage 1 toxicity including the rates of DLT and also the grades and types of toxicity, dose modifications, the duration of treatment interruptions, and the rate of permanent treatment and study discontinuations, and general consideration of efficacy including early CM mortality, CNS clearance (both the rate of clearance and the proportion who clear), and early information on the duration of remission. An additional 24 participants will be randomized to each dose of fluconazole carried into Stage 2. The Stage 2 sample size for ampho B-based regimens will depend on how many fluconazole doses were tested in Stage 1 with the intent of having a total of 48 participants treated with ampho B between the two Stages. The randomization ratio will depend on how many fluconazole doses are tested and on the target ampho B sample size in this stage.

The target sample size of a total of 48 participants on a dose of fluconazole between Stages 1 and 2, and 48 on an ampho B-based regimen is based on:

- Ensuring that the width of a 90% confidence interval (CI) for culture negativity (early discontinuation or death = fail) within a dose or within ampho B-based regimens no wider than 25%.
- Detecting a difference in EFA of about 0.10 log10 CFU/ml CSF/day (about 67% of the s.d.) between two fluconazole doses or between a dose of fluconazole and ampho B with 90% power and a 2-sided 0.05-level test.
- Detecting a 25% difference (e.g. 50% vs. 75%) in efficacy between two fluconazole doses or between a dose of fluconazole and ampho B with 90% power (one-sided alpha=.10 test).
- Having the added ability to detect unusual or unexpected events that occur at a low rate, especially in consideration of those who might not be evaluable for toxicity given very early death. For example, if an unexpected and unacceptable event occurs at a rate of 5%, there is only a 64% chance of seeing one or more rare events in 20 participants evaluable for safety and an 87% chance of seeing one or more rare events in 40 participants evaluable for safety combined over both Stages.

